#### Statistical power

Power to detect the effect of intervention after 12 months with respect to the outcome of hypertension control is simulated for the stepped-wedge study design assuming 300 practices, and an average of *μ* = 1200 or 1600 patients per practice (assuming a typical practice has 4 physicians with 300 or 400 patients per physician). For data collection months *t* = s_i_ (baseline), *s*_i_ + 3, *s*_i_ + 6, *s*_i_ +9, *s*_i_ + 12, and *s*_i_ + 18 (6 months post-intervention follow-up), power calculations are based on practice-month summaries consisting of 1800 binomial observations (6 × 300). Power is determined by simulating data from a model similar to model (1) but, for simplicity, assuming no temporal trend:2$$ \mathrm{logit}\left\{E\left({Y}_{\mathrm{i}\mathrm{t}}/{N}_{\mathrm{i}\mathrm{t}}\Big|{b}_{\mathrm{i}0},{b}_{\mathrm{i}1}\right)\right\} = {\beta}_0 + {b}_{\mathrm{i}0} + {\beta}_2{X}_{\mathrm{i}2} + {\beta}_3{X}_{\mathrm{i}\mathrm{t}3} + {b}_{\mathrm{i}1}t $$where *X*_it3_ = 0 if *t* = s_i_; *X*_it3_ = (*t* – s_i_)/12 for *s*_i_ < *t* ≤ *s*_i_ + 12, and *X*_it3_ = 1 for *t* = *s*_i_ + 18. This model assumes a linear logistic trend during the active intervention period and a constant slope during the maintenance period equal to the 12-month intervention effect. Additionally, model (2) specifies a practice-specific intercept and slope assumed to be normally distributed with means 0 and variances *σ*_0_^2^ = 0.42, *σ*_1_^2^ = 0.32 and covariance *σ*_01_ = −0.15, values estimated from preliminary pretest-posttest data on 19 medical practices (not shown). Primary interest is in exp(*β*_3_), the practice-specific odds ratio of having a positive outcome (e.g., blood pressure controlled) after 12 months intervention relative to baseline. The number of patients in the i-th practice assumed to be constant across time (*N*_i_ = *N*_it_ for all *t*) was randomly selected from *N*_i_ ~ *N*(*μ*, *μ*^7/4^) to account for expected variability in practice size. A complete data set is then generated using model (2) with (*β*_0_ = 0.50, *β*_2_ = 0.05, *β*_3_ = 0.05) corresponding to a baseline of 62 % blood pressure control for least ready practices. The fraction of times that *H*_0_: *β*_3_ = 0 is rejected with two-sided *α* = 0.05 Wald tests under the correctly specified model was taken to be the simulated power for detecting a non-null odds ratio *β*_3_. When the true *β*_3_ = 0, the results represent simulated type I error, which is seen to be close to the nominal 0.05 significance level. The stepped-wedge design has excellent power for the outcome, percentage of hypertensive patients with controlled blood pressure (see Additional file 1).

#### Aim 2: Evaluate the effect of primary care practice support on patient-level health outcomes

Our primary hypotheses are that primary care practice support will improve the percentage of patients in a practice who indicate that their provider (a) always communicated well with them during the visit, and (b) involved them a lot of the times in shared decision-making about their medications. Our secondary hypotheses are that primary care practice support will decrease (a) the percentage of patients within a practice who were hospitalized for a cardiovascular disease-related condition, (b) the percentage of patients within a practice who were hospitalized for a cardiovascular disease-related condition or died, and (c) race-based disparities in CVD-related hospitalizations and mortality. We will explore whether primary care practice support improves the percentage of patients in a practice whose tobacco use status and overall cardiovascular risk were assessed, whose blood pressure (BP) was adequately controlled, and who received appropriate management with regard to aspirin use, tobacco cessation support, and use of statin therapy.

### Statistical analysis

For the primary hypotheses, communication and shared decision-making are binomial outcomes derived from patient surveys administered at baseline (*t* = s_i_) and at the end of the intervention period (*t* = s_i_ + 12). The model to assess improvement in these outcomes is a simplification of model (1) because there are only two repeated outcomes:3$$ \mathrm{Logit}\left({\uppi}_{\mathrm{i}\mathrm{t}}\right) = {\beta}_0 + {b}_{\mathrm{i}0} + {\beta}_1{X}_{\mathrm{i}1} + {\beta}_2{X}_{\mathrm{i}2} + {\beta}_{12}{X}_{\mathrm{i}1}{X}_{\mathrm{i}2} + {g}_1\left({t}^{*};\uppsi \right) + {b}_{\mathrm{i}1}t + {\beta}_3{X}_{\mathrm{i}\mathrm{t}3} $$where *X*_it3_ = 1 if *t* = s_i_ + 12 (end-of-intervention period) and *X*_it3_ = 0 if *t* = s_i_ (baseline). Note that exp(*β*_3_) is the odds ratio of a positive response (e.g., always communicated well, involved them in shared decision-making a lot of the time) after 12 months of intervention relative to the odds of a positive response at baseline, controlling for secular trends via ψ. The average causal effect of 12 months of intervention versus the control condition will be calculated as the average difference in proportions as described for Aim 1.

For the secondary hypothesis, model (2) will apply to claims data for the percentage of patients (a) hospitalized for a cardiovascular disease-related condition and (b) hospitalized for a CVD-related condition or died. For these outcomes, *X*_it3_ = 1 if *t* = s_i_ + 18 (6 months post-intervention) and *X*_it3_ = 0 if *t* = s_i_ (baseline). To assess whether primary care practice support decreases race-based disparities in these outcomes, the binomial data will be obtained for each race and practice and time point. Other facility-level patient outcomes are given in Table 4. Model (3) will be fitted to all binomial outcomes (e. g., percentage of patients…) using SAS Proc GLIMMIX. For continuous outcomes (e.g., a 10-year CVD Risk), an identity link function leading to a linear model fitted with SAS PROC MIXED will be used with variance weight 1/*N*_it_ where *N*_it_ is the observed number of patients in the *i*-th practice at the *t*-th month.

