#### Claims data

We will use claims data at baseline, end-of-intervention, and 6 months post-intervention to assess hospitalizations for cardiovascular-related conditions, in-hospital deaths, and mortality for patients seen at participating practices (innovation effectiveness). We will have access to claims data on 85 % of the insured population in NC, specifically those covered by Blue Cross Blue Shield of North Carolina, the State Employee Health Plan, Medicare, and Medicaid. Outcomes will be aggregated to the practice level. For the baseline period, we will examine claims data for the year prior to the intervention. Following the intervention, we will examine available claims during and after the intervention for each practice.

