In the last 12 months, did you and your provider talk about starting or stopping a prescription medication? If yes, complete the rest of the questions.		Response options
PCMH7	When you talked about starting or stopping a prescription medicine, how much did your provider talk about the reasons you might want to take a medicine?	Not at all, a little, some, a lot
PCMH8	When you talked about starting or stopping a prescription medicine, how much did your provider talk about the reasons you might NOT want to take the medicine?	Not at all, a little, some, a lot
PCMH9	When you talked about starting or stopping a prescription medicine, did your provider ask you what you thought was best for you?	Yes, no

Items from Consumer Assessment of Healthcare Providers and Systems (CAHPS) patient-centered medical home supplement [19]

In addition, we will assess patients’ healthcare utilization and mortality using claims data. We will measure hospitalizations for stroke, acute myocardial infarction, and angina identified via primary diagnoses and in-hospital mortality for these conditions. For patients covered by Medicare and Medicaid, we will also be able to assess non-hospital related mortality. We will also collect clinical data on patients’ blood pressure, cholesterol levels, smoking status, and CVD risk based on the ASCVD risk calculator developed by the American Cardiology Foundation and the American Heart Association (see Table 6). These clinical data will be extracted and summarized by the CCNC Informatics Center.

**Table 6 Tab6:** Practice-level patient outcomes

Outcome	Measure
Communication	Percentage of patients who answered “always” to all 6 communication questions
Shared decision-making (SDM)	Percentage of patients who answered “a lot” and “yes” to all 3 SDM questions.
Hospitalizations	Percentage of patients hospitalized for stroke, MI, angina.
In-hospital mortality	Percentage of patients hospitalized for stroke, MI, angina who died in the hospital.
Blood pressure	Percentage of patients with BP <140/90, <140/90 if 18–59 years, <150/90 if 60–85 years.
Systolic blood pressure	Percentage of patients with a SBP <140; mean (SD), median (IQR) SBP
Diastolic blood Pressure	Percentage of patients with DBP < 90; mean (SD), median (IQR) DBP
Low-density lipoprotein (LDL) level	Percentage of patients with LDL levels in the following categories: <100 mg/dL; 100 to <160 mg/dL; 160 mg/dL or more

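### Aim 2 claims outcomes: follow-up window not matched to the one-year baseline, and two conflicting models named, so the size and direction of bias are undetermined

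*Protocol article*

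**What the plan says.** The secondary hypotheses of Aim 2 are that practice support lowers the percentage of a practice's patients with a CVD hospitalization, and the percentage hospitalized or dead. Table 6 defines the hospitalization measure as "Percentage of patients hospitalized for stroke, MI, angina", with no reference to time at risk.

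The Claims data section sets the assessment points: "We will use claims data at baseline, end-of-intervention, and 6 months post-intervention to assess hospitalizations for cardiovascular-related conditions". It fixes the first window: "For the baseline period, we will examine claims data for the year prior to the intervention". For the rest it says: "Following the intervention, we will examine available claims during and after the intervention for each practice". No length is given.

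The Aim 2 Statistical analysis section then says: "For the secondary hypothesis, model (2) will apply to claims data for the percentage of patients" hospitalized, or hospitalized or dead. X_it3 is 1 at s_i+18 and 0 at s_i. A few sentences later it says: "Model (3) will be fitted to all binomial outcomes". Model (2) comes from the Aim 1 Statistical power section, where it is introduced as similar to model (1) "but, for simplicity, assuming no temporal trend".

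**The concern.** A percentage of patients with at least one event rises with the length of the window in which events are counted. If follow-up is longer or shorter than the baseline year, the difference goes straight into the coefficient of X_it3, because every follow-up observation has one window length and every baseline observation has another. Nothing in the binomial model can take it out.

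Separately, if model (2) is used as named, the analysis is an uncontrolled before-after comparison. Any change in admission rates over the intervening 18 months is then credited to the intervention. That defeats the control of secular trends that the Limitations section claims for the stepped-wedge design.

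At stake are the hospitalization and mortality hypotheses, which bear most directly on the article's argument that cardiovascular events will be prevented. The race-disparity analysis uses the same outcomes and time points.

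**Working it through.** **1. The plan's own figure.** There is none to reproduce. The article gives no event rate, effect size or power for the claims outcomes. The risks below are assumptions, shown as a range.

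**2. Window length, no intervention effect.** Let p12 be the 12-month risk. Under a constant hazard the risk over w months is p(w) = 1 − (1 − p12)^(w/12), and the odds ratio against baseline is OR = [p(w)/(1 − p(w))] / [p12/(1 − p12)].

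Example with p12 = 2%:
- 18 months: p = 1 − 0.98^1.5 = 0.0298, OR = 1.508.
- 6 months: p = 1 − 0.98^0.5 = 0.0101, OR = 0.497.

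| Assumed 12-month risk | 6 vs 12 months | 12 vs 12 months | 18 vs 12 months |
|---|---|---|---|
| 0.5% | 0.499 | 1.00 | 1.502 |
| 1% | 0.499 | 1.00 | 1.504 |
| 2% | 0.497 | 1.00 | 1.508 |
| 3% | 0.496 | 1.00 | 1.512 |
| 5% | 0.494 | 1.00 | 1.520 |
| 10% | 0.487 | 1.00 | 1.541 |

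A simulation with 300 practices, 1,200 patients each and the article's intercept variance of 0.42 gave within-practice odds ratios of 0.495, 0.999 and 1.514 for the three windows.

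**3. Unequal risk between patients.** With gamma frailty of variance v, p(t) = 1 − (1 + v·r·t)^(−1/v), with t in years and r set to give the assumed 12-month risk. For 12-month risks of 1% to 5%, the 18 vs 12 month odds ratio falls to 1.37–1.47 (v = 10) or 1.28–1.44 (v = 20). The bias shrinks but does not vanish.

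**4. Missing trend, equal windows.** With an assumed change of 3% to 5% a year over 1.5 years, the rate ratio under no effect is 0.97^1.5 = 0.955 or 0.95^1.5 = 0.926 (falling), and 1.03^1.5 = 1.045 or 1.05^1.5 = 1.076 (rising). This is much smaller than the window effect.

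**5. The two models.** Model (2) contains readiness, X_it3, and a random intercept and slope. It has no calendar function g1 and no region term. The random slope has mean zero, so it cannot absorb a common trend. Model (3) adds region, region by readiness, and g1(t*). The claims percentages are binomial, so both statements apply to them and they cannot both hold.

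**6. Would model (3) alone be enough?** Start months are 9, 11 and 12 (50 practices each) and 14 and 16 (75 each). Baseline points therefore fall in months 9–16 and s_i+18 points in months 27–34, with no overlap. Within a readiness stratum the variance of start month is 1.556 (high) or 1.000 (low), averaging 1.278. The 18-month gap contributes 9² = 81. The variance inflation of X_it3 with a linear calendar trend and readiness is 1 + 81/1.278 = 64, ignoring clustering. With a linear spline knotted at months 16 and 27, X_it3 is not identified.

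**The case against.** The strongest reply is that the article never says the s_i+18 percentage accumulates every claim since s_i. It lists separate assessments, and Table 1 even allows a 12-month post-intervention time point. A reader might infer that follow-up is 18 months and that a null effect would therefore appear as about 50% higher odds. On that reading, a true 25% rate reduction at 2% annual risk would give p = 1 − 0.98^1.125 = 0.0225 and OR 1.13, an apparent harm. The documents do not support this as fact. It is one possible reading, and a window covering only months 12 to 18 would bias the result the other way, towards false benefit.

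A reader might also infer that the trend is deliberately left out. That is not established either. Model (2) was written for a power simulation with a graded X_it3, whereas the claims outcomes are given a two-level X_it3 as in model (3). A wrong equation number is at least as plausible. One could instead confine the later sentence to the other outcomes it follows, but then the claims outcomes would have no trend term at all.

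Finally, an article may leave exact claims windows to a fuller document. That excuses missing detail. It does not excuse a fixed one-year baseline set against whatever later claims are available, compared as a raw percentage, or two incompatible model statements in one paragraph.

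**Conclusion.** The point holds in this form: the baseline window is fixed and the follow-up window is not, no person-time term corrects for the difference, and the model is stated in two incompatible ways. The odds ratio under no effect could lie anywhere from about 0.5 to about 1.5 depending on the window chosen, and is 1.0 only if the windows match. These figures assume a constant hazard and 12-month risks of 0.5% to 10%; strong patient heterogeneity pulls the 18-month figure down to about 1.3 to 1.5.

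The window effect and the trend question are separate. Naming model (3) would settle the contradiction, but it would not remove the window bias. It also would not reliably separate trend from effect when only s_i and s_i+18 are used. The outcomes are secondary, so the analysis should be corrected before claims are extracted, but the point is not of must-fix rank.

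**What to change.** - **Windows.** Define equal 12-month windows, for example the year before s_i and s_i+6 to s_i+18. Alternatively, model events with a log person-time offset. Equal windows drop some claims months. The offset keeps them but changes the effect measure from an odds ratio to a rate ratio, so the hypothesis wording would need to follow.
- **Model.** Replace the reference to model (2) with one named model that includes calendar trend and region, and make the later sentence on binomial outcomes agree with it.
- **Calendar support.** Build the claims data by calendar period, so that control and intervention practices contribute at common times. By the stated start months, such overlap exists only between months 9 and 16. The estimate at s_i+18 will still lean on the assumed form of the trend, and the plan should say so.

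The cost is a few sentences of text, a revised claims query and a less precise trend-adjusted estimate. No new enrolment is needed.

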#### EHR/informatics

We will obtain performance data on the ABCS measures (implementation effectiveness) and patients’ intermediate clinical outcomes (innovation effectiveness) from the EHR. The ABCS measures and clinical outcomes will be collected at baseline, during the intervention (quarterly), at the end of the intervention, and post-intervention (6 and 12 months follow-up). The EHR will also supply race/demographic data. EHR data will be routed to the CCNC Informatics Center, where the data will be extracted, normalized, and placed in a standard report used for the evaluation and sent back to the practices.

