#### Statistical analysis

The statistical analysis of the primary outcomes for Aim 1 will be based on a generalized linear mixed model (GLMM) for longitudinal binomial data at the practice level. Allowing for the number of patients who are observed within a practice to vary across time, the models will be estimated by maximizing the pseudo-likelihood, specifying practices as clusters, and using empirical variance estimators. For example, the number of hypertensive patients whose blood pressure is under control *Y*_it_, out of *N*_it_ hypertensive patients, will follow a binomial (*N*_it_, *π*_it_) distribution where, conditional upon a practice-specific random intercept *b*_i0_ and slope *b*_i1_, π_it_ = *E*(*Y*_it_/*N*_it_|*b*_i0_,*b*_i1_) is the expected proportion of hypertensive patients whose blood pressure is controlled within the *i*-th practice in the *t*-th month; *t* = s_i_ (baseline), s_i_ + 3, s_i_ + 6, s_i_ +9, s_i_ + 12, s_i_ + 18 (6 month post-intervention follow-up), and for some practices s_i_ + 24 (12 month post-intervention follow-up). The GLMM is1$$ \mathrm{Logit}\left({\uppi}_{\mathrm{i}\mathrm{t}}\right) = {\beta}_0 + {b}_{\mathrm{i}0} + {\beta}_1{X}_{\mathrm{i}1} + {\beta}_2{X}_{\mathrm{i}2} + {\beta}_{12}{X}_{\mathrm{i}1}{X}_{\mathrm{i}2} + {g}_1\left({t}^{*};\uppsi \right) + {b}_{\mathrm{i}1}t + {g}_2\left(t;\uplambda \right){X}_{\mathrm{i}\mathrm{t}3} + {g}_3\left(t;\uptheta \right){X}_{\mathrm{i}\mathrm{t}4} $$where *X*_i1_ = 1 indicates east region and 0 for west region; *X*_i2_ = 1 indicates higher readiness and 0 for lower readiness stratum; *g*_t_(*t*^*^;ψ) is a smooth spline function of calendar time (*t*^*^) for the secular trend corresponding to the control condition with finite dimensional parameter ψ; *X*_it3_ = 1 indicates the active (12 months) intervention period versus 0 otherwise and *g*_2_(*t*; λ) is function for four piecewise conjoined linear segments each of 3 months duration with λ being the vector of slope parameters; *X*_it4_ = 1 is an indicator for the maintenance period versus 0 otherwise and *g*_3_(*t*;θ) is a function for two piecewise conjoined linear segments the first of 6 months duration to which all practices will contribute data and the second 6 months durations to which only a subset of practices will contribute data as determined by the stepped-wedge design. Finally, *b*_i0_ and *b*_i1_ are assumed to be bivariately normal random variables with respective variances *σ*_0_^2^ and *σ*_1_^2^ and covariance *σ*_01_. Primary interest is in the treatment effect describing the log odds of a randomly sampled patient in a practice having the outcome 12 months post-intervention relative to the log odds of a randomly sampled patient from the same practice having the outcome during the pre-intervention period; this log odds ratio is well-defined as a function of λ parameters. Finally, the average causal effect of 12 months of intervention will be calculated as the average difference in proportions, Σ_i_[E(*Y*_it_/*N*_it_|*b*_i0_,*b*_i1_,*t* = s_i_ + 12)—E(*Y*_it_/*N*_it_|*b*_i0_,*b*_i1_*t* = s_i_)]/300; a 95 % confidence interval will be determined by bootstrapping. The random coefficients logistic model (1) will be fitted using SAS Proc GLIMMIX.

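### Aim 2 gives EHR outcomes read six or seven times a model coded for two readings, and gives claims outcomes a model with no calendar trend, so the maintenance readings (EHR) and the end-of-intervention reading (claims) have no term

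*Protocol article*

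**What the plan says.** Under Aim 2, Statistical analysis, model (3) is introduced for the two survey outcomes. It "is a simplification of model (1) because there are only two repeated outcomes". Its indicator X_it3 is 1 at s_i + 12 and 0 at s_i, and it has no X_it4 term.

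The next paragraph covers the remaining Aim 2 outcomes:
- Claims: "model (2) will apply to claims data for the percentage of patients" hospitalized, or hospitalized or died, with X_it3 = 1 at s_i + 18 and 0 at s_i.
- Binomial outcomes: "Model (3) will be fitted to all binomial outcomes".
- Continuous outcomes: an identity link, "leading to a linear model fitted with SAS PROC MIXED" and weighted by N_it.

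The paragraph points to Table 4 for the other patient outcomes. Table 4 holds the communication questions; the outcome list is Table 6.

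The EHR/informatics section sets the reading schedule: ABCS measures and clinical outcomes are "collected at baseline, during the intervention (quarterly), at the end of the intervention, and post-intervention (6 and 12 months follow-up". The Aim 1 analysis gives the same times as s_i, +3, +6, +9, +12, +18 "and for some practices s_i_ + 24 (12 month post-intervention follow-up". The Claims data section takes claims at baseline, end of intervention and 6 months after it.

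**The concern.** The reason given for model (3), that there are only two readings, is true of the survey and false of the EHR outcomes. Followed as written, the model has no value of X_it3 at +3, +6, +9, +18 or +24. An analyst must either drop those readings or invent a coding.

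Elsewhere the article adds terms when readings are added. Model (1) has g2 and g3, model (4) keeps g2 for monthly ratings, and model (6) adds X_it4 for the +18 reading. Only the Aim 2 EHR outcomes get a model without terms for their own schedule.

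Two things are at stake. First, no effect beyond month 12 can be estimated for systolic and diastolic pressure, LDL category or 10-year risk, although the trial has a maintenance period and plans readings in it. Second, the two-reading contrast separates the intervention from the calendar trend poorly, which matters in a stepped-wedge trial that relies on that separation.

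The claims outcomes have a related problem. Model (2) was introduced under the Aim 1 power calculation as a simplification without a temporal trend, and it has no region term. Using it for analysis would test secondary hypotheses without secular-trend adjustment.

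**Working it through.** **1. Count of readings.** The Aim 1 power section gives 6 × 300 = 1,800 practice-month observations, which reproduces. Model (3) codes 2 × 300 = 600.
- Six readings per practice: 1 − 600/1,800 = 66.7% have no X_it3 value.
- Seven readings in every practice: 1 − 600/2,100 = 71.4%.
- Seven readings in half the practices (assumed, since the share is not given): 1 − 600/1,950 = 69.2%.

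Maintenance readings with a term: 0 of 1, or 0 of 2.

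**2. Which outcomes are affected.** Hypertension control is an Aim 1 primary outcome under model (1), where every reading has a term. Most process measures explored in Aim 2 ("whose blood pressure (BP) was adequately controlled, and who received appropriate management") also repeat Aim 1. Systolic and diastolic pressure, LDL category and 10-year risk have no other model.

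**3. Calendar overlap.** The start months in the Research design section are 9, 11, 12 (high readiness) and 14, 16 (low readiness or late). The stated allocation gives 50, 50, 50, 75 and 75 practices. Baselines fall in months 9 to 16 and end readings in months 21 to 28, so none coincide. The quarterly readings do overlap: the +3 reading of a month-9 starter falls in month 12, the baseline of a month-12 starter.

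**4. Variance inflation with two readings, linear trend and readiness.** Calendar month is s_i + 12·X_it3.
- Variance of start month, high readiness: (81 + 121 + 144)/3 − (32/3)² = 1.556. Low readiness: 1.000. Average: 1.278.
- Variance of 12·X_it3: 144 × 0.25 = 36.
- Inflation: 1 + 36/1.278 = 29.2 (R² = 0.966).

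**5. Comparison with six readings.** SE(12-month effect) is the square root of the relevant diagonal of (Σ D_i′V⁻¹D_i)⁻¹. Here V = 0.42·J + 0.32·tt′ − 0.15·(t1′ + 1t′) + σ_e²·I, with t in years from the start. The components are those of the Aim 1 power section. Taking the slope variance per 12 months and σ_e² = 0.42 are assumptions.

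| Readings and effect shape | Inflation, linear trend | SE, linear trend | SE, cubic trend |
|---|---|---|---|
| Two readings | 29 | 0.46 | 0.54 |
| Six, ramp then plateau (shape of model (2)) | 7 | 0.12 | 0.20 |
| Six, free effect at each reading (as g2 and g3 allow) | 17 | 0.40 | 0.41 |

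With σ_e² = 0.1 and a linear trend, the SE is 0.39 with two readings, 0.06 with the ramp and 0.37 with free effects. A ramp fitted to readings up to +12 only gives an inflation of 15 and an SE of 0.41 (σ_e² = 0.42). Most of the large gain in the ramp row therefore comes from assuming that the +18 effect equals the +12 effect.

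**6. Variance components, continuous outcomes, two readings.** With t = 0 and 12 in every practice and equal residual variance, there are three moments for four parameters (rank 3 of 4). The Aim 1 section defines t as study month, and the five start months then give rank 4. Practice sizes that vary, with the N_it weight, also give rank 4. Relative SEs of σ_0², σ_1² and σ_01 at σ_e² = 0.42:
- two readings, study-month t, equal sizes: 1.56, 0.79, 2.57
- two readings, months from start, sizes varying as in the power section: 0.28, 0.64, 0.75
- six readings, months from start, equal sizes: 0.12, 0.16, 0.28

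**7. Claims.** Readings are at s_i, +12 and +18, but the stated coding covers s_i and +18. Model (2) has a readiness term but no g1, no region and no region-by-readiness term.

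**The case against.** The affected outcomes appear in no primary or secondary Aim 2 hypothesis, and the trial's declared main contrast is baseline against 12 months, which model (3) does estimate. An article may also leave the coding of interim readings for such outcomes to the full plan. The first part stands and limits the weight of the point. The second does not fully answer it, because the article states a model and a reason for it, and the reason does not fit the data described.

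A reader might infer that the continuous model is not identified, or that its standard errors are invalid. The documents do not support that. With study-month t or varying N_it, all four variance parameters are identified, though weakly. Even in the rank-3 case, two readings determine the 2 × 2 marginal covariance, and the SE of β_3 depends on that, not on how it splits into components.

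A reader might also infer that hospitalization is to be reported from both model (2) and model (3). The claims outcomes are assigned to model (2) first, and the model (3) sentence follows a reference to the other outcomes. The word all is loose there, not evidence of a double analysis. Choosing +18 as the claims contrast is a stated choice and not an error in itself.

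**Conclusion.** The mismatch is real, and the sponsor should correct it. For systolic and diastolic pressure, LDL category and 10-year risk, 67% to 71% of planned readings, and all maintenance readings, have no term in the stated model. It would be wrong to conclude that these readings are lost for hypertension control, which Aim 1 covers, or that any primary hypothesis is affected.

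The cost in separating effect from calendar trend is clear in direction, but its size depends on the effect shape. Inflation falls from 29 to 7 under a ramp and plateau, and from 29 to 17 with the free terms of model (1). At the assumed residual variance the SE under those free terms falls only from 0.46 to 0.40 (linear trend) or from 0.54 to 0.41 (cubic). The firmer gains from all readings are an estimable maintenance effect, less sensitivity to the form of the trend, and better determined variance components.

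For claims, the stated model omits the calendar trend and region, and its coding leaves out the end-of-intervention reading.

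**What to change.** In Aim 2, Statistical analysis:
- Analyse the EHR-based Table 6 outcomes with model (1), or its identity-link version for continuous outcomes, using all readings with g2 and g3.
- Restrict model (3) to communication and shared decision-making.
- State one model for the claims outcomes that keeps the calendar trend and the region-by-readiness terms and has separate terms for the +12 and +18 readings.
- Correct the Table 4 reference to Table 6.

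The cost is a change of wording and a little more analysis work. No data beyond those already planned are needed. Blood pressure control may still be reported under both aims.
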